| Methodology | Single centre, parallel arm randomised controlled trial. Following informed consent, participants will be randomised to 3 cycles of treatment or no treatment. Primary outcome is live birth rate.  Each month participants will be asked to record the first day of their menstrual period. On the relevant cycle day according to the test instructions they will start doing daily LH monitoring using a quantified validated test (same brand) until a positive result is seen. 24hrs later they will start 400mg bd progesterone (Cyclogest) pessaries (vaginal or rectal) and continue these for 14 days. After 7 days they will attend for a serum progesterone level blood test. They will then check a urine pregnancy test (validated, same brand) on the 14^th^ day after starting cyclogest (15^th^ day after LH surge). They will discontinue the progesterone if hcg is negative and those who are pregnant will continue progesterone for 38 days. 2 weeks later they will be offered an early pregnancy ultrasound.  We will gain consent to check NHS records to record live births 42 weeks after the positive pregnancy test. We will ask patients to contact us if they have a miscarriage or late pregnancy loss but will not contact them to chase for information as this does not directly impact on our measurable outcomes (clinical pregnancy rates and live birth rates). |
| Research Sites | Homerton University Hospital |
| Objectives/Aims | To assess whether luteal support with progesterone pessaries affects the likelihood of clinical pregnancy and/or live birth in natural cycles for couples with unexplained infertility |
| Number of participants/patients | 200 in total – 100 in the test group and 100 in the control group |
| Main Inclusion Criteria | Female:   - bilateral patent tubes within last 12 months (HSG/HyCoSy/Laparoscopy) - Ovulation as defined by regular cycles or ultrasound appearance of either a corpus luteum or dominant follicle or midluteal progesterone over 30nmol/ml - Regular intercourse and failure to conceive for at least 12 months   Male:   - Semen analysis with: - >15 mil/ml concentration - Motility over 40% - Progressive motility over 32% - ≥ 4% normal forms - No erectile dysfunction or other problem preventing penetrative intercourse |

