**Methodology:**

Study design:

This study is a prospective, pragmatic, two-armed, randomised controlled trial. The hypothesised benefit of the luteal phase progesterone support is to enhance endometrial receptivity and improve conception rates measured as clinical pregnancies and eventually live births.

The study does not aim to validate different formulations of progesterone or different dosing regimens. The design of the trial supports the use of progesterone as it is licensed to be used in ART cycles, at a dose of 400mg twice per day either vaginal or rectal application.

This trial will recruit eligible participants meeting the criteria for a diagnosis of unexplained infertility. All new patients seen in the fertility units will be screened for eligibility and if eligible, will be invited to participate. Following informed consent from both partners, participants will be randomised in a 1:1 ratio to either the treatment or control groups. Women will remain in the trial for three menstrual cycles and will be followed up to the end of the third cycle. If pregnant, the outcome of the pregnancy will be recorded at 6-7 weeks of pregnancy when a scan will be performed to determine clinical pregnancy and subsequently by following up live births within 6 weeks postpartum.

Study Population:

The trial will recruit and randomise 200 participants.

Study setting:

Single centre trial at the Homerton Hospital NHS trust Fertility Unit

Inclusion Criteria:

Female:

- Bilateral patent tubes within last 12 months (HSG/HyCoSy/Laparoscopy)
- Ovulation as defined by regular cycles or ultrasound appearance of either a corpus luteum or dominant follicle or midluteal progesterone over 30nmol/ml
- Regular intercourse and failure to conceive for at least 12 months

Male:

- Semen analysis with:
- >15 mil/ml concentration
- Motility over 40%
- Progressive motility over 32%
- ≥ 4% normal forms
- No erectile dysfunction or other problem preventing penetrative intercourse

Exclusion criteria:

- Age ≥42 (as likely component in infertility),
- Unilateral tubal patency
- BMI ≥30
- Abnormal uterine cavity as seen on 3D ultrasound

Primary outcome:

Live birth rates

Secondary Outcome:

Biochemical pregnancy rates (positive urine HCG test at least 14 days after starting progesterone)

Clinical pregnancy (intrauterine gestational sac confirmed on ultrasound at 6-8 weeks gestation)

Mid-luteal serum progesterone levels

Clinical efficacy outcomes/clinical safety outcomes:

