Participants in the control arm will record the time of their LH surge and perform a home pregnancy test 14 days later if their next menstrual period has not started.

All participants will be asked to attend the hospital for a mid-luteal serum progesterone test 7 days after the LH surge is detected in the first cycle only.

Monitoring Adherence

Follow-up:

Participants will be asked to email a trial-specific, secure NHS.net email address with details of their cycles – dates for LH positive results and menstrual period start dates. They will use their trial number rather than identifiable personal data. They will have consented to being contacted by either telephone or email to remind them and ask for their data. They will be reminded a maximum of twice per cycle and if they do not respond it will be assumed that they have withdrawn from the trial.

Start dates of each cycle and each LH surge will be recorded. Participants will attend the phlebotomy department at the Homerton for their mid-luteal progesterone and will have consented to the trial team accessing their records to obtain the result.

Data Collection:

The following data will be collected:

Results from hormone profile and tubal patency tests and semen analysis will have been checked prior to consent – this information would be accessed by the clinical team regardless as part of their clinical care.

Basic demographic data, fertility/ menstrual/gynaecological history, relevant medical history, allergies and medication history, dates of menstrual cycles and LH surges and clinical outcomes.

This data is routinely recorded in a patient’s notes and consent will be obtained to access this. Dates of menstrual cycle and LH surges will be requested from patients during the trial.

Identifiable data will be stored in a password protected recruitment log at site but data entered into the database will be pseudo-anonymised (identified only by a participant’s trial ID).

Participant withdrawal:

Participants will have the option to withdraw at any point during the trial and can do so by contacting the team either by email or telephone.

If at any point during the trial, a participant does not reply to two consecutive requests for results it will be assumed that they have withdrawn and no further attempts at contact will be made.

End of Study Definition:

This will be the date six weeks after the expected date of delivery of the last patient randomised who has an ongoing pregnancy.

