**Results Analysis**

Sample size

According to a randomised controlled trial comparing expectant management with stimulated cycle IUI treatment over 3 cycles, 7% of the expectant management group reported live births compared to 24% of the treatment group^7^. The study identified that gave progesterone supplementation in natural cycles also showed a 24% clinical pregnancy rate (live birth rate was not reported).

Using a baseline expected live birth rate of 7% and an expected live birth rate of 24% in the treatment group, with an α0.05 and 80% power, we need to recruit 70 participants to each group. Assuming a drop out rate, we will aim to recruit 100 per group, as was recruited in the Farquhar trial.

Method of Analysis

We have adequate statistical analysis experience within the research team to analyse the data.

Analyses will be intention-to-treat, will include all randomised participants and will analyse according to the treatment group to which they were randomised. For each analysis we will present treatment effect (risk ratio)) along with a 95% confidence interval and a two-side p-value. A P value of <0.5 will be considered statistically significant.

Baseline demographic data will be assumed to be equivalent between the two groups due to the randomisation process.

For each of the outcomes measured (livebirth rate, biochemical pregnancy rates, clinical pregnancy rate, mid-luteal serum progesterone levels and pregnancy loss rates) we will perform a logistic regression, initially doing a univariable regression for each of the potential confounders AMH level, 3 vs no ovulatory cycles according to LH kits, antral follicle count, parity) and combining these together with a variable representing group using lasso or stepwise regression we will perform a multivariable logistic regression analysis.

We will validate the model, looking at calibration and discrimination by providing the c-statistic equivalent to the area under the ROC curve.

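### A covariate listed as a confounder, three versus no LH-kit ovulatory cycles, is counted after randomisation and is partly a consequence of conceiving

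*Protocol*

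**What the plan says.** In the Protocol, Results Analysis (Method of Analysis), the candidate confounders are "AMH level, 3 vs no ovulatory cycles according to LH kits, antral follicle count, parity". The model is then described as "combining these together with a variable representing group using lasso or stepwise regression we will perform a multivariable logistic regression analysis". It applies widely: "For each of the outcomes measured (livebirth rate, biochemical pregnancy rates, clinical pregnancy rate, mid-luteal serum progesterone levels and pregnancy loss rates". The same section commits to intention-to-treat, to including everyone randomised, and to a risk ratio with confidence interval and p-value. It ends by asking for calibration and a c-statistic.

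Three other places fix when LH-kit data arise:

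- The Methodology row of the summary table says of each month on trial: "On the relevant cycle day according to the test instructions they will start doing daily LH monitoring".
- Study Procedures (Follow-up and Data Collection) says "Start dates of each cycle and each LH surge will be recorded" and "Dates of menstrual cycle and LH surges will be requested from patients during the trial".
- Methodology (Study design) sets the window: "Women will remain in the trial for three menstrual cycles and will be followed up to the end of the third cycle".

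Ovulation at entry is established by other means: "Ovulation as defined by regular cycles or ultrasound appearance of either a corpus luteum or dominant follicle or midluteal progesterone". LH kits play no part in eligibility.

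**The concern.** A confounder must precede treatment. This variable follows it. A woman who conceives in cycle 1 or 2 and carries to birth moves to pregnancy follow-up and adds no further LH cycles, so she cannot be classed as having three. If progesterone works, treated women reach three less often because they have conceived. Entering the count beside treatment group therefore conditions on something that the outcome and the treatment have helped to produce.

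Three things are at stake:

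- **Power.** The covariate takes up variation that belongs to the outcome itself.
- **Interpretation.** The adjusted treatment effect has no clear meaning, and the model would report that more ovulation goes with fewer births.
- **Discrimination.** The c-statistic is inflated by a predictor that encodes the outcome.

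There is also a coding gap. Three versus none leaves women with one or two cycles unclassified, which conflicts with the section's own rule that everyone randomised is analysed.

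**Working it through.** **Inputs from the Protocol (Results Analysis, Methodology).** Live birth 7% (control) and 24% (treatment) over three cycles; alpha 0.05; 80% power; 70 per group needed, 100 per group recruited; 1:1 allocation; two-sided test.

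**Assumptions not in the Protocol.** The chance of a live-birth conception is constant across cycles. LH testing stops at such a conception. A surge is detected in a share q of cycles, with q from 0.80 to 0.98. Significance is judged at 0.05, as in the sample-size statement.

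**1. The plan's own figure.** With p̄ = (0.07 + 0.24)/2 = 0.155,

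n = [1.96·√(2·0.155·0.845) + 0.8416·√(0.07·0.93 + 0.24·0.76)]² / 0.17² = (1.003 + 0.419)² / 0.0289 ≈ 70 per group.

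This reproduces the stated 70. At 100 per group the power is about 92%. The planned odds ratio is (0.24/0.76)/(0.07/0.93) = 4.20.

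**2. Births that cannot have a count of three.** The per-cycle chance is h = 1 − (1 − P)^(1/3).

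- Control: 1 − 0.93^(1/3) = 2.39%. Treatment: 1 − 0.76^(1/3) = 8.74%.
- Share of live births conceived in cycles 1–2 is [1 − (1 − h)²]/P. Control: 0.0472/0.07 = 67%. Treatment: 0.1672/0.24 = 70%.

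Per 100 women this is about 4.7 of 7 births in control and 16.7 of 24 in treatment. In the limit of perfect detection with no withdrawals, every woman without a live birth has three cycles, and every woman with fewer than three has a live birth.

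**3. Effect of the covariate, coded three versus fewer.** Exact cell probabilities give the odds ratios. Power comes from 1,500 simulated trials of 100 per arm at each q, with conception occurring only in surge-detected cycles.

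| q | Covariate OR | Covariate significant | Treatment OR with covariate | Power without → with |
|---|---|---|---|---|
| 0.80 | 0.25 | 86% | 4.06 | 92% → 90% |
| 0.90 | 0.13 | >99% | 4.03 | 93% → 87% |
| 0.95 | 0.07 | 100% | 4.01 | 93% → 83% |
| 0.98 | 0.03 | >99% | 3.98 | 93% → 72% |

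If a conception can instead occur in a cycle whose surge was missed, the covariate odds ratio is 0.18, 0.11, 0.06 and 0.03 at the same four values of q. Over both versions and repeated runs, power without the covariate is about 92–94%, power with it is about 70–92%, and the treatment odds ratio with it is about 4.0–4.2.

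**4. If women with one or two cycles were dropped.** Under the version in the table, the births left are those with three surges.

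- q = 0.80: (7 × 0.206 + 24 × 0.185)/31 = 5.88/31 = 19%.
- q = 0.98: (7 × 0.312 + 24 × 0.290)/31 = 9.14/31 ≈ 30%.

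**The case against.** The best defence is that the regression may not be the trial's main comparison. The section promises an intention-to-treat risk ratio first. The regression that follows, with univariable screening, lasso or stepwise selection, calibration and a c-statistic, reads like prognostic modelling, and a logistic model does not yield the promised risk ratio. This stands in part. A reader might infer that the covariate breaks the randomised comparison, but the unadjusted risk ratio does not use it. The Protocol does not say which analysis is primary, however, and it prescribes the regression with treatment group for each outcome.

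The covariate is also a candidate, not a forced term. That helps little, because it was significant in about 85–100% of simulated trials.

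Three further readings go too far:

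- **Power below 50%.** Dropping women with one or two cycles gives 47% power even at perfect detection. The Protocol nowhere states such a deletion, and it would contradict the rule that everyone randomised is included. The wording may be loose drafting for three versus not three.
- **No births, hence separation, in the zero-cycle group.** This needs a missed kit result to rule out conception, which no document says. If it does not, that very small group consists mostly of early conceptions.
- **A count fully determined by the outcome.** Missed surges, anovulation and withdrawal also lower it, a cycle 3 conception can have three, and the Protocol does not say whether counting resumes after an early loss.

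Finally, with no treatment effect and 90% detection, simulated type I error with the covariate was 3–6%. On these assumptions, no excess of false positives is created.

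**Conclusion.** The point holds, in bounded form. The Protocol names as a confounder a variable that is recorded after randomisation and that an early successful conception prevents from reaching its upper category. The timing and the direction follow from the Protocol's own text and do not depend on the assumed detection rate. The sizes do: they rest on a constant per-cycle chance, on the planning rates, and on a detection rate that the Protocol does not give.

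The harm is lost power (slight at 80% detection, about 20 percentage points at 98%), an adjusted effect that cannot be interpreted, and an inflated c-statistic. It is not a large bias in the treatment odds ratio, and it leaves the unadjusted intention-to-treat risk ratio intact. The missing category for one or two cycles is a separate drafting fault in the same phrase.

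**What to change.** In Method of Analysis, delete the LH-kit cycle count from the list of covariates. State that adjustment uses only variables fixed before randomisation: AMH, antral follicle count and parity, which are already listed, taken at their baseline values. Report the number of LH-positive cycles by arm as a descriptive table. Carry the same list into the statistical analysis plan.

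The cost is one phrase removed and one sentence added. No new data are needed, and the sample size does not change. The change should be made before outcome data are analysed.

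### The described model lets lasso or stepwise selection act on the treatment term, yields odds ratios where risk ratios are promised, and cannot fit serum progesterone

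*Protocol*

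**What the plan says.** All of this stands in the Protocol, Results Analysis, under Method of Analysis.

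- Population: "Analyses will be intention-to-treat, will include all randomised participants", by allocated group.
- Effect measure: "For each analysis we will present treatment effect (risk ratio)) along with a 95% confidence interval and a two-side p-value".
- Model: one method is given for five outcomes, namely live birth, biochemical pregnancy, clinical pregnancy, progesterone and pregnancy loss. The end of that list reads "mid-luteal serum progesterone levels and pregnancy loss rates) we will perform a logistic regression".
- Model building: univariable fits come first, for four candidates ("AMH level, 3 vs no ovulatory cycles according to LH kits, antral follicle count, parity"). The next step is "combining these together with a variable representing group using lasso or stepwise regression we will perform a multivariable logistic regression analysis". Calibration and a c-statistic follow.

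The Trial Objectives section describes the progesterone objective as a difference in levels between the arms. The Methodology section lists serum levels as a secondary outcome and gives no cut-off for it.

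**The concern.** The sequence of univariable screening, selection, calibration and c-statistic is a way to build a prediction model. The trial's question is a different one: how much treatment changes the live birth rate between randomised groups. For that, the treatment term has to be in the model whatever the data show, and its estimate and interval have to be reported whether or not it is significant.

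As written, group goes into the same lasso or stepwise step as the confounders, and nothing protects it. Three consequences follow for the model as described.

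1. The treatment effect can be removed or, under lasso, pulled toward the null. Standard lasso supplies no confidence interval or p-value, and ordinary ones after stepwise selection ignore the selection.
2. The coefficient is a log odds ratio, while the promised measure is a risk ratio. No conversion is described.
3. One of the five listed outcomes is not binary and cannot be fitted at all.

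The primary estimate is at stake. Two analysts following this paragraph could choose different algorithms and report different treatment effects, or one of them none.

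**Working it through.** **Inputs.** From the Protocol, Results Analysis: live birth rates of 7% for control and 24% for progesterone; the size, stated as "with an α0.05 and 80% power, we need to recruit 70 participants to each group"; a two-sided p-value; a target of 100 per group; four candidate confounders, so five terms with group. I use 0.05 two-sided, as in the sample size; the significance threshold in the analysis text is printed as 0.5.

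**Step 1: reproduce the plan's own figure.** Two proportions, pooled variance under the null, no continuity correction:

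n = [1.960·√(2·p̄·(1−p̄)) + 0.842·√(p₀(1−p₀) + p₁(1−p₁))]² / (p₁−p₀)²

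With p₀ = 0.07, p₁ = 0.24 and p̄ = 0.155:

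- √(2·0.155·0.845) = 0.512, times 1.960 = 1.003
- √(0.0651 + 0.1824) = 0.497, times 0.842 = 0.419
- n = (1.422)² / 0.0289 ≈ 70 per group

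The stated 70 is reproduced. It is the size for a direct comparison of two proportions, with no covariates and no selection, so the sample size and the described model do not correspond. At 100 per group the same formula gives 91.9% power.

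**Step 2: scale of the effect measure.**

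- Risk ratio = 0.24 / 0.07 = 3.43
- Odds ratio = (0.24/0.76) / (0.07/0.93) = 4.20
- Odds ratio / risk ratio = 0.93 / 0.76 = 1.22

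At the planning rates the two measures are not interchangeable.

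**Step 3: information available for selection.**

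| Analysed per arm | Expected live births | Births per candidate term (5 terms) |
|---|---|---|
| 100 | 24 + 7 = 31 | 31 / 5 = 6.2 |
| 70 | 0.31 × 70 = 21.7 | 21.7 / 5 = 4.3 |

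With so few events per term, the set of terms kept is likely to be unstable.

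**Step 4: described model against promised result.**

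| Item | Promised or defined | Described model |
|---|---|---|
| Treatment term | Effect, interval and p-value for each analysis | Inside lasso or stepwise; not stated to be forced in or unpenalised |
| Live birth, pregnancy and loss outcomes | Risk ratio | Odds ratio; no conversion described |
| Serum progesterone | Difference in levels | Binary logistic regression; no cut-off given |

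On the last row, a level of 30 does appear in the Introduction and in the inclusion criteria, but as evidence of ovulation. Nothing applies it to the outcome.

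**The case against.** **The sentence is loose.** The authors may have meant to select among the confounders and then add group. That is possible, and one clause would settle it. It would not settle the odds ratio or progesterone points, which stand on either reading.

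**The risk ratio can be obtained.** A reader might infer that the plan cannot deliver its risk ratio. The text does not support that. A crude ratio from the two-by-two table fits the intention-to-treat sentence, and a logistic model can be standardised to give one. The regression could then be an additional adjusted analysis. What stands is that neither route is described and no analysis is named as primary. The 22% gap would mislead only if an odds ratio were reported as a risk ratio, which the protocol does not say it will do.

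**Loss of the treatment term may be no more than non-significance.** Largely true for stepwise with a 0.05 retention rule. At 24% against 7% and 100 per arm, a plain comparison already fails in about 8% of trials (100% − 91.9%), so a count of how often group is dropped mostly restates power. Any shrinkage figure for lasso depends on a penalty that the protocol does not give. I therefore attach no frequency or size to this harm. What remains is that a non-significant trial would yield no model-based estimate or interval.

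**Covariates and baseline balance.** A reader might also fault the absence of female age from the candidates, or the sentence "Baseline demographic data will be assumed to be equivalent between the two groups due to the randomisation process". Leaving out a prognostic covariate does not bias a randomised comparison, and a baseline table is a reporting detail. Neither is part of this point.

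**A statistical analysis plan may resolve it.** The Trial Committees section foresees one. But the protocol does not leave the method open here: it fixes one, and a plan that followed it would inherit the conflict.

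**Conclusion.** The point holds as a conflict within one section. The protocol promises a risk ratio with interval and p-value for each analysis, and then describes a single model that does not itself give one, does not protect the treatment term, and cannot be applied to one of its five outcomes.

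The progesterone and scale limbs follow directly from the text; at the planning rates the scale difference is 4.20 against 3.43. The selection limb rests on the literal reading of the model-building sentence. Its direction is clear (removal, or shrinkage toward the null under lasso, with invalid ordinary inference afterwards), but its size cannot be fixed because no retention rule or penalty is stated. The event counts assume that the planning rates hold and that all 100, or all 70, per arm are analysed.

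The documents do not show that the risk ratio is unobtainable or that treatment will in fact be lost. They do leave the primary analysis of live birth unnamed, and the only model on offer is unsuited to it. That should be corrected before analysis.

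**What to change.** Reword the model paragraph in Method of Analysis:

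- **Primary analysis.** Name the intention-to-treat risk ratio for live birth, with 95% confidence interval and two-sided p-value. Treatment is always in the model and unpenalised. The ratio may be unadjusted, or come from modified Poisson regression with robust standard errors or from standardised logistic regression, using a short set of baseline covariates fixed in advance. The number of ovulatory cycles by LH kit is observed during the trial cycles and so does not belong in a baseline set.
- **Other binary outcomes.** Use the same method.
- **Selection steps.** Remove univariable screening and lasso or stepwise from the treatment-effect analysis. If a prediction model is still wanted, with its calibration and c-statistic, label it secondary and exploratory.
- **Serum progesterone.** Analyse as continuous with a linear model, on the log scale if skewed, and report a difference in means or a ratio of geometric means.

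The cost is one reworded paragraph. No extra participants, visits or data items are needed.
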